### Analyses

#### Clinical analyses

Our primary (base-case) analyses will be performed according to the intention-to-treat principle, including data from all participants regardless of whether they received the intervention or not. For the analyses we will use SPSS statistical software and Excel (for the bootstraps). Respondents for whom at least 75% of the data per measurement instrument are available will be included in the analysis. Missing data on item level will be handled using SPSS missing value analysis. Completely missing measurements will be handled using multiple imputation. Analysis will include comparisons of the intervention groups (brief sex counselling, sexological treatment and waiting list) as well as more complicated multi-level analysis. The accuracy of the findings will be expressed in terms of 95% confidence intervals.

To test the main research questions, difference scores for all outcome variables will be calculated and compared between the three intervention groups using MANOVA. In the case of significant multivariate results, subsequent univariate analysis using independent groups t-tests will be conducted to assess the significance of differences pre/post intervention between control and experimental groups.

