### Participants

The patient population we aim to investigate consists of adolescents with sexual problems. Patients are eligible to participate if they meet the following criteria: age between 18 and 25 years old; at least mild to moderate sexual problems (based on Questionnaire for the Screening of Sexual Dysfunction [29,30], International Index of Erectile Function (men) [31] and Female Sexual Functioning Index (female) [32]); no severe psychiatric co-morbidity or relational problems, and the sexual problems are not caused by disease, medication use or physical disabilities.

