#### Sexual functioning

##### Questionnaire for the Screening of Sexual Dysfunctions

The Questionnaire for the Screening of Sexual Dysfunctions (QSSD) [29,30] is a self-report instrument with 70 items, each assessed using a 5-point or a 7-point Likert-scale, which aims to measure the presence (and level) of sexual difficulties. This instrument has different versions, dependent on gender, partnered status and gender of the partner. Anchor points used are 'almost never' and 'always' for frequency and 'no trouble' and 'very much trouble' for associated distress.

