##### International Index of Erectile Function

The International Index of Erectile Function (IIEF) [31] is a multidimensional self-report instrument with 15 items, assessed using a 6-point Likert-scale, meant to measure male sexual functioning on the dimensions of erectile functioning, orgasmic functioning, sexual desire, intercourse satisfaction and overall satisfaction. A high score indicates healthy erectile functioning. Its sound psychometric properties have been proven [31].

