##### Treatment Satisfaction Questionnaire

The Treatment Satisfaction Questionnaire (TSQ) is a new instrument, derived from the Erectile Dysfunction inventory of Treatment Satisfaction (EDITS), and adjusted so it would fit the total study population [53]. This instrument measures the satisfaction of the participants with the treatment as a whole and the different aspects of the treatment. The reliability and validity of de EDITS were well established.

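### The MANOVA that tests the main questions takes in all outcome variables, but FSFI is collected only in women and IIEF only in men, so read jointly it has no complete cases

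*Protocol article*

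**What the plan says.** All references are to the protocol article.

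- **Main test (Clinical analyses).** For the main research questions, "difference scores for all outcome variables will be calculated and compared between the three intervention groups using MANOVA".
- **Gate (same section).** "In the case of significant multivariate results, subsequent univariate analysis using independent groups t-tests will be conducted". The pairwise tests therefore depend on the multivariate result.
- **Sex-specific instruments (Participants).** Eligibility uses the QSSD together with the "International Index of Erectile Function (men) [31] and Female Sexual Functioning Index (female) [32". The IIEF section describes that scale as "meant to measure male sexual functioning on the dimensions of erectile functioning", among others. The FSFI section describes its female counterpart. Both stand under Sexual functioning, the first group in Outcome measures.
- **Common instrument (QSSD section).** The QSSD goes to both sexes, but "This instrument has different versions, dependent on gender, partnered status and gender of the partner".
- **Treatment satisfaction (Secondary outcomes).** "This instrument measures the satisfaction of the participants with the treatment as a whole and the different aspects of the treatment".
- **Missing data (Clinical analyses).** "Completely missing measurements will be handled using multiple imputation".
- **Primary outcome (Abstract).** It is how severe the sexual problems are. No single instrument is named for it.

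**The concern.** A MANOVA tests a vector of dependent variables and needs every component of that vector for each participant it uses. The plan fixes the vector as the difference scores of all outcomes, and that set includes two scales that nobody has together. It also includes, if taken at its word, a scale that rates a treatment not yet given at baseline.

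The main research questions and the primary construct are at stake. If the multivariate test cannot be run, the rule that opens the t-tests cannot operate either. The analyst would then have to drop scales, split by sex or build a composite, and nothing in the article says which. That choice could fall after the data are seen, and it bears on the outcome that matters most.

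**Working it through.** The plan gives no figure on this point to reproduce. The check is a count of complete vectors, followed by a comparison of sections.

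**Inputs**
- Randomised: 150 per condition × 3 = 450 (Sample size; Abstract).
- Planned as analysable: 95 per group × 3 = 285 (Sample size).
- FSFI in women only, IIEF in men only (Participants; the two instrument sections).
- Sex ratio: not given, and not needed for the main count.

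**Step 1: complete vectors.** Let W be the number of women and M the number of men, with W + M = 450 and no other data missing.
- FSFI difference score available: W.
- IIEF difference score available: M.
- Both available: 0, because no participant belongs to both groups.

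The result is 0 of 450, and likewise 0 of 285, for every value of W. Deleting incomplete rows from a simulated set of 450, with about 60% women assumed, also left 0 rows.

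**Step 2: which variables empty the vector.**
- Without IIEF: W participants remain, all women.
- Without FSFI: M participants remain, all men.
- Without either: all 450 remain.

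FSFI and IIEF alone therefore cause the failure. The other instruments shared by both sexes (QSSD, CES-D, BSI, SF-36) do not.

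**Step 3: the covariance.** MANOVA also needs the within-group covariance of every pair of dependent variables. FSFI and IIEF are never observed in the same person, so their covariance cannot be estimated from the data.

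**Step 4: the TSQ.** A pre/post difference score needs a value before treatment. A rating of treatment received has none in any arm, so the TSQ cannot supply the quantity that the MANOVA takes in.

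**Step 5: does a common score repair it?** For sex s with baseline mean m(s) and baseline SD sd(s), define z = (x − m(s)) / sd(s), where x is the FSFI total in women and the IIEF total in men. The difference score is then

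(x_post − m(s)) / sd(s) − (x_pre − m(s)) / sd(s) = (x_post − x_pre) / sd(s).

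It exists for W + M = 450 participants. Both scales run in the same direction, since the article says that high scores mean healthy function on each, so no reversal is needed.

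**The case against.** The strongest reply is that the literal reading cannot be the intended one. The text does not say one MANOVA and does not list the dependent variables. Taken literally, all outcomes would include the demographic questionnaires, which stand under Secondary outcomes. The sentence is tied to the main research questions, which concern sexual and general mental health. Recruitment writes IIEF/FSFI as alternatives for one slot, and the QSSD already covers both sexes. Multi-level analyses are also planned. An article may leave the scoring to a fuller document.

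Part of this stands. The joint analysis is the natural reading, not a quoted word. The TSQ is a secondary outcome and may never have been meant for the main test. But limiting the sentence to the main questions does not remove FSFI and IIEF, because sexual function is central to those questions. The article is also not silent here. It states the variables, their form, the method and the groups, and that rule cannot be run. A fuller plan would have to replace it. No section splits by sex, defines a common score or narrows the set.

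Three stronger readings are tempting and are not supported:

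- **That the plan would invent FSFI scores for men and IIEF scores for women.** Nothing says so. The imputation sentence ordinarily means a questionnaire that was due and not completed, and a scale that does not apply to a person's sex was never due. One sentence would settle it.
- **That the waiting list never has TSQ data.** That is certain only for the 26 weeks without treatment. These participants may then choose a treatment, assessments run to 12 months, and the schedule (Additional file 1) is not shown.
- **That power is lost through separate analyses by sex.** The plan proposes no such split and gives no sex ratio, and its sample size rests on a repeated-measures MANOVA. No power figure follows from the documents.

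**Conclusion.** The point holds. With FSFI and IIEF both in the outcome vector, complete cases number 0 of 450, and the gatekeeping test of the main research questions cannot be computed as written. This rests on one assumption, that the outcomes enter jointly. It does not depend on the sex ratio, the effect size or the amount of missing data. The TSQ is a separate, smaller error in the same sentence: it has no baseline and so no difference score.

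The finding is limited to how the main test is specified. It does not show that the trial is underpowered or that its data are unusable. The shared instruments can be analysed now, and a usable sexual-function measure can be built from what is already collected.

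**What to change.** Before analysis:

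1. Define one sexual-function severity score available in both sexes. Either use the FSFI total for women and the IIEF total for men, each standardised by its own baseline mean and SD, or use the QSSD severity score standardised within version. Name the choice.
2. Analyse that score in one model for both sexes, with sex as a covariate.
3. In the joint MANOVA, put the score in place of the separate FSFI and IIEF scales, and remove the TSQ.
4. State that multiple imputation applies only to instruments that were due for that participant.

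The cost is analysis wording and one derived variable, with no new data. The downside is that a standardised composite is less directly interpretable than the scales themselves, so report FSFI in women and IIEF in men as supportive results.

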**Methods:**

In a randomised controlled trial we will compare (1) brief sex counselling with (2) intensive sexological treatment, and (3) delayed treatment (waiting list). Embedded in this RCT will be a trial-based economic evaluation, looking at the cost-effectiveness and cost-utility of brief sex counselling versus the two other interventions. Four hundred fifty adolescents (aged 18-25) with sexual problems will be recruited among the persons who visit the Public Health Service (PHS) and through various websites. After a screening procedure, eligible participants will be randomly allocated to one of the three intervention groups. Primary outcome measure of the clinical evaluation is the severity of sexual problems. Other outcomes include psychological distress, especially depression. The economic evaluation will be performed from a societal perspective. Costs will be assessed continuously by a retrospective questionnaire covering the last 3 month. All outcome assessments (including those for the economic evaluation) will take place via the internet at baseline, and at 3, 6, 9, and 12 months after baseline.

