#### Effectiveness study

1. Does brief sex counseling as envisaged, when compared to delayed treatment, improve the sexual and general mental health of adolescents and young adults? To which extent (effect size) and in what respect (which outcome dimensions)?

2. Is brief sex counseling efficacious, when compared to delayed treatment, in preventing escalation of (sexual and mental) health problems compared with no help?

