### Sample size

In a repeated-measures analysis of the within-between-interaction effect, a sample size of 95 in each group has a power of 95% to detect an effect size of 0.41 using repeated-measures MANOVA with a 0.050 two-sided level of significance. In the absence of published controlled studies on professional care for young people with sexual problems, we set the desired effect size at d = 0.40, representing the central point of the range of effect sizes that are considered as 'medium size' [54]. N = 150 per condition is deemed necessary to guarantee the required number of respondents, in view of the expected non-response after inclusion and later attrition [55]. In a repeated-measures analysis of the within-subjects effect, a sample size of 86 in the treated group has a power of 95% to detect an effect size of 0.25 using a repeated-measures MANOVA with a 0.050 two-sided level of significance. The before mentioned N = 150 per condition is expected to guarantee the required number of participants.

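### The primary outcome can be tested only after an all-outcome, three-arm MANOVA is significant; this gate can only lower its power and gives limited protection against false positives

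*Protocol article*

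**What the plan says.** The abstract's Methods paragraph declares one primary outcome: "Primary outcome measure of the clinical evaluation is the severity of sexual problems". Under Research Questions, Effectiveness study, the first question is: "Does brief sex counseling as envisaged, when compared to delayed treatment, improve the sexual and general mental health of adolescents and young adults". The second question concerns the same pair of arms.

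The Clinical analyses section sets out how the main research questions are tested: "difference scores for all outcome variables will be calculated and compared between the three intervention groups using MANOVA". The next sentence makes the follow-up conditional: "In the case of significant multivariate results, subsequent univariate analysis using independent groups t-tests will be conducted". These t-tests are described as comparing control and experimental groups. The section gives no significance level, order or adjustment for them. It also mentions comparisons of the groups "as well as more complicated multi-level analysis", but ties the latter to no outcome or contrast.

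The Sample size section says that "a sample size of 95 in each group has a power of 95% to detect an effect size of 0.41", using a repeated-measures MANOVA "with a 0.050 two-sided level of significance". On the target effect it adds: "we set the desired effect size at d = 0.40". It recruits 150 per condition to allow for non-response and attrition.

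**The concern.** A trial with one declared primary outcome and one main contrast would normally test that contrast first and on its own. Here the contrast can be declared significant only if a joint test over all outcomes and all three arms succeeds first. Outcomes that do not respond add degrees of freedom to that joint test without adding signal, so a real effect on sexual problems can go undeclared because of scales that are not primary.

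The gate also offers less protection than it seems to. It guards against false positives when no outcome differs anywhere. Once one outcome truly differs, the gate tends to open, and the t-tests on the remaining outcomes have only their own level to protect them. A false claim on depression would matter beyond the clinical paper, because decrease of depressive symptoms is also an effect measure in the cost-effectiveness ratio.

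**Working it through.** **Inputs from the protocol article.** Three equal arms; 95 per arm analysed and 150 recruited; two-sided 0.05; d = 0.40 (0.41 in the power statement); five measurements (baseline, 3, 6, 9 and 12 months).

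**Assumptions.** The number of outcomes p in the MANOVA is not stated, so p = 6 and p = 10 are used. Difference scores have SD 1 and pairwise correlation ρ of 0.3 or 0.5. Both active arms have the same effect d over the waiting list, measured in SDs of the difference score.

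**1. The plan's own figure.** For a repeated-measures MANOVA interaction with 3 groups and 5 measurements, N = 285:
- df1 = 2 × 4 = 8 and df2 = 2 × (285 − 3 − 4 + 2) = 560.
- With f = d/2 = 0.205, λ = f² × df2 = 0.042025 × 560 = 23.5, and power is 0.954. The smallest n for 95% is 94 per group.

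The stated 95 is therefore reproducible, although the d-to-f conversion is assumed. It belongs to this interaction test, not to the difference-score procedure in Clinical analyses.

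**2. Direct test of brief versus delayed.** Two-sample t-test, noncentrality d√(n/2):
- n = 95: 0.40 × √47.5 = 2.76, power 0.783 (0.803 at d = 0.41).
- n = 150: 0.40 × √75 = 3.46, power 0.932 (0.943 at d = 0.41).

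**3. The gate.** Success requires both a significant MANOVA and a significant t-test. The probability of both cannot exceed the probability of the t-test alone, so the direction of the effect on power is certain.

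For three groups, Wilks' Λ gives an exact F = [(1 − √Λ)/√Λ] × (N − p − 2)/p on 2p and 2(N − p − 2) degrees of freedom. With p = 6 and N = 285 these are 12 and 554. The noncentrality is n × (2/3) × d² × c, where n × (2/3) × d² = 95 × 0.667 × 0.16 = 10.13 and c depends on which outcomes respond:
- Only the primary: c = (1 + 4ρ)/[(1 − ρ)(1 + 5ρ)] = 1.257 (ρ = 0.3) or 1.714 (ρ = 0.5), giving 12.7 or 17.4.
- Three of six: c = 3/(1 − ρ) − 9ρ/[(1 − ρ)(1 + 5ρ)] = 2.743 or 3.429, giving 27.8 or 34.7.
- All six: c = 6/(1 + 5ρ) = 2.400 or 1.714, giving 24.3 or 17.4.

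The gate is thus hardest to pass when only the primary outcome responds or when strongly correlated outcomes all move together. It is easiest to pass when about half respond.

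**4. Simulated power for brief versus delayed on the primary outcome** (4,000 trials per setting in the main runs, Monte Carlo standard error at most √(0.25/4000) = 0.8 points):

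| Setting | Direct | Through the gate |
|---|---|---|
| 95 per arm, only primary responds, p = 6 | 78–79% | 56–67% |
| 95 per arm, only primary responds, p = 10 | 78–79% | 46–62% |
| 95 per arm, half of the outcomes respond, p = 6 | 79% | 77–78% |
| 95 per arm, all respond equally, p = 6 to 10 | about 78% | about 60–76% |
| 150 per arm, only primary responds, p = 6 to 10 | about 93% | about 74–90% |

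The result also depends on the third arm. If only the primary outcome responds and the intensive arm has half the effect (d = 0.41 and 0.205, p = 4 to 8, 95 per arm), gated power is 42–64% against 80% direct.

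**5. False positives.** When nothing differs in any arm, the simulated family-wise error is about 5%, so the gate works there. Now let only the primary outcome respond, with p = 6, 95 per arm, and t-tests at 5% without adjustment. The chance of at least one false positive is:
- brief versus delayed only (6 − 1 = 5 true nulls): about 16%;
- both active arms versus waiting list (12 − 2 = 10 true nulls): 27–28%;
- all three pairs (18 − 2 = 16 true nulls): 36–37%.

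**The case against.** The first effectiveness question also asks on which outcome dimensions counselling works, so a multivariate test is an understandable choice. The follow-up t-tests do reach each outcome, so a reader who infers that the primary outcome is never tested goes too far: it is tested, but conditionally.

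A reader might also infer that the family-wise error is uncontrolled as a matter of fact. The documents do not support that. The article states no level and no adjustment for the t-tests, but it is a condensed account, and an analysis plan not shown may supply one. Moreover, the t-tests are described as between control and experimental groups, which may exclude brief versus intensive; the 36–37% figure applies only if all three pairs are tested.

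Nor can the largest power loss be read as the expected one. It assumes no effect on any other scale, whereas the protocol predicts linked effects on depression and measures several neighbouring sexual constructs. If half the outcomes respond, the loss is close to nil. At the full 150 per arm it is also smaller, about 3 to 10 points with 6 outcomes when only the primary responds. Imputation does not restore lost information, so the truth for a trial with attrition lies between the results for 95 and 150.

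These points limit the size of the problem. They do not remove the gate, which is a stated decision rule. The multi-level analysis does not replace it, because it is assigned to no outcome or contrast.

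**Conclusion.** The point holds in a limited form. As written, the declared primary outcome can be declared different between brief counselling and delayed treatment only behind a significant MANOVA over all outcomes and three arms. That this cannot raise power, and will generally lower it, is certain. The size is not: at 95 per arm and d = 0.40 it runs from almost nothing to roughly 30 points (about 78% to 46%) when both active arms work equally well, depending on the number of outcomes, their correlation and which of them respond, none of which the article fixes.

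The false-positive part is conditional. The gate protects the complete null. If the t-tests turn out to be unadjusted and only the primary outcome responds, the risk with 6 outcomes at 95 per arm is about 16% to 37%, according to the pairs tested.

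**What to change.** In Clinical analyses, remove the MANOVA condition for the primary outcome. Name one severity score that every participant has. The article does not name one, and the FSFI is for women and the IIEF for men, so neither can serve alone. A QSSD score is a candidate, provided that its versions for gender, partnered status and gender of the partner yield a common scale.

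Test brief versus delayed on that score directly at two-sided 5% at 6 months, which coincides with the end of the 26-week waiting period, after which the delayed arm may choose treatment. Under the plan's d = 0.40, this test has about 78% power at 95 per arm and 93% at 150.

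Treat all other outcomes and contrasts as secondary, with 95% confidence intervals and either a prespecified order or a Holm adjustment. The choice between these is the trial team's. A MANOVA may remain as a secondary, descriptive analysis of the outcome profile.

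The cost is a change of analysis wording, with no effect on recruitment, visits or treatment. The downside is that secondary outcomes face a stricter threshold.

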### Outcome measures

Several instruments will be used to assess the effects of brief sex counselling on sexual functioning, depression and other psychological and physical complaints, and on secondary outcomes. Furthermore instruments will be used to assess the cost-effectiveness of brief sex counselling from a social perspective. The outcomes will be measured before randomization (during initial screening), at baseline and at 3, 6, 9 and 12 months after baseline (Additional file 1).

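### The main test compares pre/post difference scores, but none of the four post-baseline assessments is named as post, and the sample size describes a different test

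*Protocol article*

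**What the plan says.** All references are to the protocol article.

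- **Clinical analyses.** The main questions are tested on difference scores for all outcomes, compared across the three arms by MANOVA. Only if the multivariate result is significant, "subsequent univariate analysis using independent groups t-tests will be conducted to assess the significance of differences pre/post intervention". No month and no significance level is given for these t-tests.
- **Outcome measures.** Data are collected before randomisation, then "at baseline and at 3, 6, 9 and 12 months after baseline".
- **Sample size.** The calculation is for another procedure: "In a repeated-measures analysis of the within-between-interaction effect, a sample size of 95 in each group", "using repeated-measures MANOVA with a 0.050 two-sided level of significance". The target is stated without a time point: "we set the desired effect size at d = 0.40".
- **Abstract, Methods.** The primary outcome is the severity of sexual problems, also without a time point.
- **Research Questions, Effectiveness study.** Both questions compare brief counselling with delayed treatment. Neither names a month.
- **Delayed treatment.** The waiting list lasts 26 weeks. After that the participant may choose either active treatment.
- **Randomisation and procedure.** Assessment emails are tied to the end of treatment and the start of follow-up. This second clock is not mapped to the months from baseline.

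**The concern.** A difference score needs one defined end point. Here there are four candidates, and the arms run for different lengths: at most three sessions, at most ten sessions, or 26 weeks of waiting. *Post intervention* could therefore fall at different calendar times in different arms.

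Two things are at stake. The first is the estimand. At 3 months and about 6 months the contrast is brief counselling against untreated delay, which is what the effectiveness questions ask. At 9 and 12 months the comparator may already have had brief counselling or intensive treatment. The second is error control. If the result is positive at one assessment and null at another, nothing in the article says which one decides.

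**Working it through.** **1. The plan's own figure.** The article says "a sample size of 95 in each group has a power of 95% to detect an effect size of 0.41". It gives neither the number of measurements nor their correlation. As a plain two-group comparison, n per group = 2(1.960 + 1.645)²/d² = 25.99/d². This gives 155 at d = 0.41 and 163 at d = 0.40. With 95 per group and d = 0.41, power is 80.7%. For a change score the variance is multiplied by 2(1 − r), where r is the pre/post correlation. Then r = 0.69 gives 96 per group and r = 0.70 gives 93. So 95 fits a single pre/post test only if r is about 0.69 to 0.70, which is not stated. None of the repeated-measures MANOVA settings tried (2 or 3 groups, 2 to 5 measurements, correlation 0 or 0.5, with 0.41 or 0.205 as Cohen's f) returns 95.

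The companion figure, "a sample size of 86 in the treated group has a power of 95% to detect an effect size of 0.25", does reproduce with f = 0.25, three measurements and correlation 0 (power 95.1%). Three measurements do not match the five planned, although another correlation could fit another count. The stated sizes therefore cannot be tied to a defined pre/post test.

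**2. Which assessments answer the question.** 26 weeks is 182 days, or about 6 months. Of the four assessments, 3 and 6 months fall within the waiting period or at its end; 9 and 12 months fall after it. The article does not exclude the later two from the comparison.

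**3. False positives with the MANOVA condition met.** One outcome, one contrast, no true difference, each t-test at an assumed two-sided 0.05. For m independent tests the rate is 1 − 0.95^m: 9.75% for m = 2 and 18.5% for m = 4. Repeated measures are correlated, so the rate is P(max |Z| > 1.96) for equicorrelated normal statistics, obtained by simulation:

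| Assumed correlation | 3 and 6 months | All four |
|---|---|---|
| 0.3 | 9.5% | 17.4% |
| 0.5 | 9.1% | 15.6% |
| 0.7 | 8.4% | 13.1% |
| 0.8 | 7.8% | 11.4% |

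**4. What the MANOVA condition does.** The article does not say whether one MANOVA spans all assessments or one is run at each. Both were simulated for a two-arm contrast with four outcomes, assuming between-outcome correlation 0.3 and between-time correlation 0.5 to 0.8. The figures are error rates on the primary outcome:

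| Situation | One MANOVA per time | One joint MANOVA |
|---|---|---|
| Nothing differs, four times | 4.1–5.4% | 1.6–2.2% |
| Another outcome differs (d = 0.40, n = 95), two times | 7.2–8.5% | 6.4–8.1% |
| Another outcome differs (d = 0.40, n = 95), four times | 10.6–14.5% | 7.8–12.7% |

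**5. After the fix.** One pre-specified test has 5% error. At d = 0.40 in raw SD units (the same as a change score with r = 0.5, since 2(1 − 0.5) = 1), the noncentrality is 0.40√(n/2). For n = 95 it is 2.757, giving power Φ(2.757 − 1.960) = 78.7%. For n = 150 it is 3.464, giving 93.4%. Keeping all four assessments eligible with Bonferroni (0.05/4 = 0.0125 per test) would lower these to 60.2% and 83.3%.

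**The case against.** A reader might infer that a claim can rest on any of four t-tests at full alpha. The documents do not support that:

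- The t-tests follow only a significant multivariate result. When nothing differs, this keeps the primary outcome's error near or below 5%.
- The article does not say that t-tests are repeated at each assessment, and it gives them no alpha. The 0.050 level stands only in the Sample size section.
- For the waiting-list contrast, at most two of the four assessments are untreated comparisons.
- The email schedule separates the end of treatment from follow-up, so *post* may be meant as end of treatment.

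It can also be said that a condensed article may leave alpha hierarchies over time to a fuller document.

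All of this limits the size of the problem and is accepted. It does not remove the problem. The article does state its main test, and that test rests on an undefined quantity. End of treatment is mapped to no month and differs by arm. The MANOVA covers all outcomes and three arms, so a true effect on depression, or of intensive treatment against waiting, can open the way to the t-tests.

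A reader might also conclude that 95 per group is wrong. That cannot be shown, because the correlation and the number of measurements are not given.

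**Conclusion.** The point holds as a fault in defining the main test, not as proof of uncontrolled error. No assessment is named as *post*, the sized test is not the test described in the analysis, and the choice of month decides whether the comparator is still untreated.

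The inflation is conditional. It is about 8–10% (3 and 6 months) or 11–17% (all four) if the MANOVA condition is met, each t-test is at 0.05 and the correlation is 0.3 to 0.8. It is about 6–15% when that condition is modelled with one other outcome truly differing, and near or below 5% on the primary outcome when nothing differs. The correlations, the number of outcomes and the per-test alpha are assumptions. The reading of 6 months as the end of the wait also assumes that both clocks start at about the same time.

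**What to change.** In the Clinical analyses section, state that:

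1. The primary test is the change from baseline to 6 months in the severity of sexual problems, with the instrument named, since three sexual-function questionnaires are listed. It compares brief counselling with delayed treatment, once, at two-sided 0.05.
2. This test does not depend on the all-outcome, three-arm MANOVA.
3. The 3-, 9- and 12-month comparisons are secondary and reported with 95% confidence intervals. The 9- and 12-month results carry a note that waiting-list participants may by then have been treated.

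Then restate the Sample size section for this test, with the assumed pre/post correlation and the expected attrition behind "N = 150 per condition is deemed necessary to guarantee the required number of respondents". Also say how the end-of-treatment clock in Randomisation and procedure relates to months from baseline.

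The cost is a few sentences and one recalculation, with no new data. The downside is small: an effect seen only at another assessment could not be claimed as confirmatory.
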